## Abstract

**Background and aim:**

Attempts at personalisation of exercise programmes in head and neck cancer (HaNC) have been limited. The main aim of the present study is to investigate the feasibility and acceptability of introducing a remotely delivered, fully personalised, collaborative, and flexible approach to prescribing and delivering exercise programmes into the HaNC usual care pathway.

**Methods:**

This is a single arm, feasibility study. Seventy patients diagnosed with HaNC will be recruited from two regional HaNC centres in the United Kingdom. Patients will undertake an 8-week exercise programme designed and delivered by cancer exercise specialists. The exercise programme will start any time between the time of diagnosis and up to 8 weeks after completing treatment, depending on patient preference. The content of the exercise programme will be primarily based on patient needs, preferences, and goals, but guided by current physical activity guidelines for people with cancer. The primary outcome measure is retention to the study. Secondary quantitative outcomes are uptake to the exercise programme, different measures of exercise adherence, pre- and post-intervention assessments of fatigue (Multidimensional Fatigue Symptom Inventory—Short Form), quality of life (SF-36), physical activity levels (International Physical Activity Questionnaire–Short Form), and various components of physical fitness. The outcomes of the nested qualitative study are acceptability and feasibility of the intervention evaluated via interviews with patients, health care professionals, and the cancer exercise specialists. Intervention and participant fidelity will be determined using checklists and scrutiny of each patient’s logbook and the cancer exercise specialists’ meeting notes. Analysis of quantitative data will be via standard summary statistics. Qualitative data will be analysed using thematic analysis.

**Expected results:**

This feasibility study will inform the design and conduct of a future randomised controlled trial. Success will be defined according to a traffic light system for identifying the appropriateness of progression to a randomised controlled trial.

**Trial registration:**

International Standard Randomised Controlled Trial Number registry (ISRCTN82505455).

## Introduction

### Rationale and background

Head and neck cancer (HaNC) represents malignancies arising from the larynx, hypopharynx, oropharynx, oral cavity, lips, and nasopharynx [1]. Globally, HaNC is the seventh most common cancer with over 930,000 new cases and almost 500,000 deaths annually [2]. Symptom burden is typically considerable and mainly related to the location of the cancer and its treatment, the latter of which is often aggressive and multi-modal [3]. Some symptoms are often still evident at 1-year post-treatment [4]. Notably, people with HaNC are typically frailer and more than twice as likely to report cancer-related disability than individuals with other cancers [5,6]. Identification of safe and effective interventions to help address these issues and improve the quality of life of people with HaNC is therefore an important endeavour.

Substantial scientific evidence accumulated for more than 30 years indicates that exercise is a safe, cost-efficient, and effective intervention during all parts of the cancer continuum [7]. Regular exercise can reduce symptoms such as cancer-related fatigue and depression, attenuate cancer treatment-related toxicity, help prevent and manage co-morbidities, and reduce cancer-specific and all-cause mortality [8–11]. Exercise oncology research has mostly been conducted in breast, prostate, and colon cancer, however, and HaNC has been severely underrepresented [12]. Generalising findings from other cancers is problematic, since people with HaNC often differ considerably in ways that have important implications for exercise prescription and delivery [13]. A survey of 430 people with HaNC, for example, found that HaNC-related symptoms were perceived as major barriers to engaging in exercise [14]. Specifically, dry mouth and throat, swallowing difficulties, shoulder weakness and pain, and drainage issues in the mouth or throat were ranked first, fifth, sixth, and seventh, respectively, of 37 perceived barriers to exercise. Other symptoms such as pain, depression, malnutrition, and weight loss are common to other cancers, but often more prevalent or more severe in people with HaNC [13]. This considerable symptom burden, combined with poor health literacy, high levels of social deprivation, and social isolation [15–17], likely explains the low levels of physical activity and poor cardiorespiratory fitness observed in HaNC cohorts [18,19]. Moreover, these factors make people with HaNC a hard-to-reach group for engagement in lifestyle interventions such as exercise programmes [16,20].

A survey of people with HaNC in the United Kingdom reported that many are motivated to participate in an exercise programme if such an intervention was available [14]. Physical activity is not included in the National Institute of Health and Care Excellence guidelines for improving HaNC outcomes [21], however, and exercise programmes are not currently part of usual care for HaNC in the United Kingdom. Moreover, despite their many unique issues that have important implications for exercise [13], no published physical activity guidelines currently exist on how to best prescribe exercise and promote its uptake and adherence in people with HaNC. Another notable issue is that centralisation of HaNC services in the United Kingdom has resulted in regional units serving large geographical areas. Thus, centralised service-based exercise programmes are unlikely to be an effective approach to support exercise uptake and adherence, since travel distance negatively impacts participation in an exercise programme in those with cancer [22].

A major criticism of exercise oncology research is that the individual needs of people with cancer have largely been ignored, using a ‘one size fits all’ approach to the design and delivery of exercise programmes [23,24]. Consequently, a patient-centred approach that includes personalisation of exercise programmes for people with HaNC has been limited [25–27]. This is an important issue, as preferences for the frequency, intensity, duration, type, and location of exercise, and timing of the start of an exercise programme, vary considerably among people with HaNC [14]. Studies involving mainly people with breast cancer have shown significantly better outcomes for personalised exercise programmes versus a more standardised approach [28,29]. A collaborative approach in which people with HaNC have at least equal input into the design of the exercise programme is also desirable, as this provides a high level of autonomy, which is an important determinant of exercise adherence [30]. This is consistent with the National Health Service’s long-term plan for a high level of personalisation in health and care in England, recognising that a one size fits all approach cannot meet the increasing complexity of peoples’ needs and expectations [31]. Another issue is that fluctuations in symptoms across the HaNC continuum affect the willingness, tolerance, and ability to perform exercise [32,33], which might be somewhat dependent on the type of treatment the patient is receiving or has received. It therefore seems desirable to incorporate built-in flexibility into exercise programmes, to allow patients to autoregulate their exercise in quick response to changing symptoms [34]. Built-in flexibility also should improve exercise adherence by allowing a rapid response to any changes in patient circumstances and by improving self-efficacy for overcoming barriers to exercise [35].

### Study aims and objectives

A fully personalised, collaborative, and flexible approach to exercise prescription in people with HaNC has not been investigated. Thus, the main aim of the present study is to investigate the feasibility and acceptability of introducing a remotely delivered, fully personalised, collaborative, and flexible approach to prescribing and delivering exercise programmes into the HaNC usual care pathway. This study will inform a future randomised controlled trial (RCT). Objectives are to determine:

Eligibility, exercise programme uptake, retention, and different aspects of exercise adherence.People with HaNC, health professionals’, and cancer exercise specialists’ views on acceptability, intervention components, processes, and feasibility of integrating the intervention into the usual care pathway.Intervention and participant fidelity.Frequency, intensity, time, type, and location of exercise, and timing of the start of the exercise programme, based on the current needs, preferences, and goals of people with HaNC.Suitability of outcome measures and provide data to allow a sample size calculation for a definitive RCT.

## Materials and methods

### Research design and study setting

This one arm, two-centre feasibility study, registered on the International Standard Randomised Controlled Trial Number registry (trial registration number ISRCTN82505455), will take place at two regional National Health Service HaNC centres. Aintree University Hospital, which is part of Liverpool University Hospitals NHS Foundation Trust, is located in Liverpool in the North West of England and is host to the largest single centre HaNC unit in the United Kingdom and in a geographical location that has the third highest multiple index of deprivation in England [36]. Sunderland Royal Hospital, which is part of the South Tyneside and Sunderland NHS Foundation Trust, is located in the North East of England. The Head and Neck Multidisciplinary Team serves the population of Sunderland, South Tyneside, and North Durham. Sunderland is one of the 20% most deprived districts/unitary authorities in England. Life expectancy for both men and women are lower than the average for England. Fig 1 shows the SPIRIT study timeline and data collection time points. An overview of the study design and procedures is shown in Fig 2.

**Fig 1 pone.0289911.g001:**
[figure not shown]
Spirit study timeline and data collection time points. N/A: Not applicable; MFSI-SF: Multidimensional Fatigue Symptom Inventory Short Form; SF-36: Short-Form 36 Health Survey Questionnaire; IPAQ-SF: International Physical Activity Questionnaire Short Form; ROM: range of motion.

**Fig 2 pone.0289911.g002:**
[figure not shown]
Flow diagram showing an overview of the study design and procedures.

### Participants

Patients. Seventy patients will be recruited from the two HaNC regional centres. This should provide a minimum sample size of 42 patient participants on study completion, based on a conservative estimated retention rate of 60% [15,18,26,37]. The target sample size was determined pragmatically using guidelines for feasibility studies that recommend a sample size of between 24 and 50 [38–40]. Moreover, a sample size of 40 people with HaNC for a feasibility study involving an exercise intervention has been deemed sufficient to estimate an effect size for a full trial [41].

Patient participants must meet the following inclusion criteria: 1) ≥ 16 years old; 2) able to provide informed consent; 3) diagnosed with HaNC and being treated with curative intent; 4) between the time of diagnosis and up to 8 weeks post-treatment; and 5) classified as low or medium risk according to a physical activity preparticipation risk stratification tool [42]. Patients classified as high risk according to the risk stratification tool, being treated with palliative intent, or engaging in any other intervention that may exert interference effects during their participation in this study, will be excluded from participation. The study will be as inclusive as possible, engaging adult patients with no restriction on age, socioeconomic background, ethnic diversity, or geographical location. The National Institute for Health and Care Research Equality, Diversity and Inclusion toolkit [43] will be used for increasing participation of underserved communities, such as ethnic minorities. Any patients with speech difficulties will be supported with alternative and augmentative communication methods.

Health care professionals and cancer exercise specialists. Up to 20 healthcare professionals, involved in the usual care of people with HaNC, will be consented to take part in an interview to establish their views on the acceptability, processes, and integration of the intervention into the usual care pathway. Three cancer exercise specialists, employed to design and deliver the exercise programmes, also will be invited to be interviewed.

### Recruitment

A HaNC research nurse or the treating clinician will screen potentially eligible patient participants against the eligibility criteria using weekly head and neck multidisciplinary team meetings, clinical lists, and patient medical notes. Eligible patients, who represent those newly diagnosed with HaNC, will be introduced to the study, and given participant information sheets for both the main study and the nested qualitative study during their next routine clinic appointment, between the time of diagnosis and the start of treatment. Eligible patients will be subsequently followed-up to enquire about their willingness to enrol. Although it has been recommended that exercise programmes should be included in the cancer survivorship plan as early as possible [44], many people with HaNC do not feel able to start before treatment [14]. Patients that initially decline will therefore be asked for consent to be re-approached after starting their cancer treatment and, where relevant, again at their first post-treatment consultation. Patients also will be informed that they can enrol in the exercise programme at any time between diagnosis and up to 8-weeks post-treatment and will be given instructions on how to do this. Patients will not be permitted to re-enrol in the exercise programme if they withdraw, or postpone the exercise programme once started, since the effect of timing of the start of the exercise programme on exercise adherence will be evaluated. Allowing different starting time points also allows for identification of any issues that are specific to the starting time. Patients that decline the intervention, or who withdraw from or postpone the intervention, will still be offered the opportunity to consent to participate in the nested qualitative study.

The rate and timing of enrolment onto the exercise intervention will be quantified. Reasons for refusal to enrol onto the exercise programme will be sought while respecting the right to refuse without giving a reason. Patients who provide written consent to participate will be referred to an oncology specialist physiotherapist for pre-intervention assessments and their general practitioner will be informed about their participation in the study. Patients are not expected to incur any personal expenses during any stage of the study and there will be no financial compensation for participation. The study is suitably insured against personal harm.

### Ethics

Favourable ethical opinion has been given by the West of Scotland Research Ethic Service (reference 22/WS/0058). Any protocol modifications will be approved by this committee and the sponsor will be notified. All participants will agree to participate by signing a statement of informed consent. Patients will provide separate consent for participation in the intervention and interview.

### Pre- and post-intervention assessments

Assessments will be conducted in clinic by oncology specialist physiotherapists immediately before and after the 8-week exercise programme and will consist of patient-reported outcome measures and objective measures (Table 1). After baseline assessments, patients will be referred to a cancer exercise specialist for a needs analysis and subsequent design and delivery of the exercise programmes.

**Table 1 pone.0289911.t001:** Measurement properties of the pre- and post-intervention assessments. Assessments of physical fitness will be performed in the order shown in the table in accordance with recommendations [45].

Outcome	Measurement Tool	Attributes
Fatigue	Multidimensional Fatigue Symptom Inventory—Short Form (MFSI-SF)	Comprises 30 statements or questions with a 5-point Likert-scale scoring response that assesses fatigue across five domains: 1) general fatigue; 2) physical fatigue; 3) emotional fatigue; 4) mental fatigue; and 5) vigour [46].
Health-related quality of life	Short-Form 36 Health Survey Questionnaire (SF36)	Comprises 36 questions that explore eight domains of health: 1) physical functioning; 2) role limitations due to physical health; 3) role limitations due to emotional problems; 4) energy/fatigue; 5) emotional well-being; 6) social functioning; 7) pain; and 8) general health [47].
Physical activity levels	International Physical Activity Questionnaire (IPAQ)–Short Form	Comprises seven questions that explore the amount of moderate and vigorous physical activity performed and the amount of time spent walking and sitting over the past 7 days [48].
Lower body muscular strength and endurance	30-Second Chair Stand Test	Maximum number of times within 30 s that an individual can rise from a seated position to a full stand without pushing off with the arms [45]. ICC = 0.89 [49].
Upper body muscular strength and endurance	30-Second Arm Curl Test	Maximum number of times a hand weight can be curled through a full range of motion in 30 s. Hand weight is 5 lb for women and 8 lb for men [45]. ICC = 0.81 [49].
Cervical spine and shoulder range of motion	Long-arm goniometer	Cervical spine range of motion in forward flexion, extension, lateral flexion, and rotation. Shoulder range of motion in flexion, abduction, and lateral and medial rotation [50].
Power, speed, agility, and dynamic balance	8-Foot Up-and-Go Test	Shortest time taken to rise from a seated position on a chair, walk 8 feet around a cone, and return to the chair and sit back down [45]. ICC = 0.95 [49].
Aerobic endurance	6-Minute Walk Test	Maximum distance that can be walked in 6 minutes along a 30 m course [51]. ICC = 0.94 [49].

**ICC** = test-retest intraclass correlation coefficient.

### Study intervention

The intervention is a personalised, collaborative, and flexible 8-week exercise programme, delivered remotely to address the issue of regional cancer units serving large geographical areas. Each exercise programme will be co-designed by the patient and a cancer exercise specialist and informed by a comprehensive individual needs analyses that considers each patient’s current clinical status, medications, pre-intervention assessments, exercise history, exercise preferences, perceived barriers to exercise, and personal goals. The physiotherapists will provide advice to cancer exercise specialists on any HaNC-related issues identified in the pre-intervention assessments.

Exercise programmes will be developed within the framework of current physical activity guidelines for people with cancer [34,52,53], which state they should engage in aerobic, resistance, and flexibility training [34,52,53]. This is summarised in Table 2 according to the FITT method.

**Table 2 pone.0289911.t002:** Framework used in the current study for prescribing exercise according to the FITT (frequency, intensity, time, and type) method. How appropriate patterns and progressions of exercise are to be identified are also included.

Aerobic exercise	**Frequency:** ≥ 3 days/week. **Intensity**: Moderate intensity. Where moderate intensity exercise is not feasible/appropriate due to deconditioning or current health conditions, prescribe light intensity exercise. **Time:** ≥ 30 min duration, although deconditioned/currently sedentary individuals will likely need to start with less than 30 min. Between 10 and 20 min is an appropriate starting point for these individuals. **Type:** Exercise involving large muscle groups. **Pattern:** Avoid two consecutive days with no exercise. For deconditioned/currently sedentary individuals, consider intermittent exercise to accumulate the daily prescribed exercise time. **Progression:** Should involve a maximum 5 min increase in session duration each week, as tolerated, until 30 min of continuous exercise can be performed [54]. Exercise intensity should then be increased using the exercise intensity domains for ratings of perceived exertion proposed by the American College of Sports Medicine: light = 9–11; moderate = 12–13; vigorous = 14–17 [54].
Resistance exercise	**Frequency**: ≥ 2 days/week. Advise twice per week where possible. If a participant refuses to perform aerobic exercise, advise 3 days/week. **Intensity**: 8–15 repetitions (≥ 60% 1RM). Advise 10–15 repetitions for deconditioned/currently sedentary individuals. **Time:** For deconditioned/currently sedentary individuals, prescribe 1 set per exercise for the first 2 weeks and progress to 2 sets thereafter. Rest 2–3 minutes between sets. **Type**: Dynamic exercises using both concentric and eccentric muscle actions, although a combination of dynamic and isometric exercise can be performed if isometric exercise is not contraindicated. All major muscles groups should be exercised, preferably using multijoint exercises. **Pattern:** Spread sessions evenly throughout the week, with at least 48 hr recovery before exercising the same muscle groups again. **Progression:** Use the double progressive method [55]. This initially involves increasing the repetitions within the target repetition range. Once the patient can perform the maximum number of repetitions within the target repetition range for all sets for a given exercise, with good form, the resistance is increased. When using exercise bands, the patient should be instructed on the importance of standardising hand placement on the band. Hands that are further apart on the band will increase resistance, and vice-versa. **Miscellaneous:** The resistance training programme should include 8–10 different exercises using a whole-body approach. Split routines should be avoided unless the participant has recent (within the last 4 weeks) resistance training experience, and it is inappropriate for the volume of resistance exercise to be fit into one training bout. Exercises that target specific muscles should be incorporated into the training programme where dysfunction from treatment is interfering with the ability to undertake activities of daily living. Multijoint exercises and large muscle groups should be exercised before single joint and smaller muscle groups in each exercise session.
Flexibility exercise	**Frequency:** ≥ 2 days/week on days when other exercise is being performed. **Intensity:** Stretch to a feeling of tightness or slight discomfort. **Time:** 8–10 stretches each held for 10–15 sec for maintenance stretches and 30 sec for developmental stretches. **Type:** Static stretches for major muscle groups, focusing more time on any muscles that have been found to be shorter than the normal range, especially if causing physical dysfunction.

Balance exercises also will be encouraged for any patients that present with balance issues during their initial assessments [53]. Patients’ needs, preferences, and goals will take precedence, however, if these are not congruent with current physical activity guidelines. This approach is based on the premise that the best exercises are the ones the person will do. Personalisation of exercise programmes will include appropriate manipulation of the frequency, intensity, time, type, volume, progression, and location of the exercise [54]. A menu of no-cost, convenient, locally available, or virtual exercise options, partly informed by previous research [14], will be used to help patients choose their preferred type of exercise and location. However, patients will be encouraged to suggest alternatives based on preferences and any past successes at adhering to exercise. The exercise location is therefore likely to differ based on patient preference. Whether patients exercise alone or with others also will largely depend on personal preference. Supervised group exercise sessions will not be offered due to increased expense and funding restrictions. Flexibility will be embedded into each patient’s exercise programme so that they can autoregulate the acute training variables in response to changes in symptoms and other perceived barriers to exercise [34]. Coloured elastic resistance bands (Theraband, Akron, OH) will be given to patients for performing resistance exercises. Each colour represents a different band resistance at 100% elongation (i.e., tan = 1.1 kg, yellow = 1.3 kg, red = 1.7 kg, green = 2.1 kg, purple = 2.6 kg, black = 3.3 kg, silver = 4.6 kg, and gold = 6.5 kg). Resistance bands have been shown to be a versatile and effective method for developing muscular strength and endurance compared to the use of conventional resistance training equipment such as free weights and resistance training machines [56].

Exercise programmes will be progressed towards meeting the minimum recommended amount of physical activity for people with cancer [52] where appropriate. The focus, however, will be on avoiding inactivity and promoting exercise adherence rather than meeting the physical activity guidelines as a primary goal. Exercise programmes will be progressed by manipulating only one acute training variable at a time.

Comprehensive instructions will be given to patients on how to interpret the 6–20 ratings of perceived exertion scale, according to those published by Borg [57]. An ‘ACTIOHN exercise prescription principles’ document, written specifically for this study, will be used to guide the cancer exercise specialists when writing each patient’s exercise programme and for completing fidelity checks.

Each patient will meet with a cancer exercise specialist before the exercise programme starts, to discuss the exercise programme and to obtain patient approval of its content, and for the cancer exercise specialist to provide instruction on exercise technique and provide information on safety. During the 8-wk exercise programme, a cancer exercise specialist will undertake a weekly 30-minute, individual video or telephone consultation with each patient. Consultations will provide patient education, discuss safety issues, address perceived exercise barriers, and encourage accurate and timely completion of the patient’s daily exercise log. Videos, delivered via a commercially available app (Physitrack®; Physitrack PLC, UK), will be used to help instruct patients on how to perform exercises safely and effectively. Paper copies showing photographs and written instructions for each exercise will be supplied to any patients where video access is not possible. Although all exercises will be performed by patients unsupervised, the cancer exercise specialists will check and advise on technique during weekly consultations. The cancer exercise specialists will send two texts each week to each patient to further encourage timely completion of daily exercise logs. The second text also will include a motivational message.

Behaviour change techniques to improve the patients adherence to the exercise programme will draw on the CALO-RE taxonomy [58] and will be implemented using motivational interviewing skills [59]. Behaviour change techniques and motivational interviewing will be informed by Self-Determination Theory [60]. The cancer exercise specialists have been given specialist training on behaviour change techniques relevant to physical activity and their implementation through the motivational interviewing approach. Further behaviour change support for patients will include being given written ‘top tips’ information and ‘exercise stories’ of how to best manage specific HaNC symptoms and overcome barriers to exercise. These peer-informed resources were developed by clinicians in collaboration with the Cancer of Head and Neck Group Experience (CHANGE) patient and public involvement (PPI) group. The CancerFit (www.cancerfit.me/site/) and Macmillan (www.macmillan.org.uk/cancer-information-and-support) websites, and our Twitter feed will provide online resource support.

After post-intervention assessments with the oncology specialist physiotherapist, the patient will meet with a cancer exercise specialist for a final time to develop and agree a personalised exit strategy from the 8-week exercise programme. This is to facilitate transition to independent long-term exercise and will involve discussing and formalising the patient’s goals over the next 12 months, how the current exercise programme can be progressed, and information to facilitate sustained behaviour change and how to deal with relapses. This use of an exit strategy is consistent with that recommended for exercise referral schemes in the United Kingdom [61].

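### Table 2 reverses the effect of grip width on elastic-band resistance: for the same movement, a wider grip gives less resistance, not more

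*Protocol article*

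**What the plan says.** Table 2 of the protocol article (Study intervention) is the framework for prescribing exercise. Under Progression in its resistance-exercise row, repetitions are increased first. Once the patient reaches the top of the repetition range in all sets "with good form, the resistance is increased". For bands, the row then says that "the patient should be instructed on the importance of standardising hand placement on the band", and gives the reason: "Hands that are further apart on the band will increase resistance, and vice-versa".

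The text after Table 2 says that elastic bands "will be given to patients for performing resistance exercises" and that "Each colour represents a different band resistance at 100% elongation". It lists eight colours, from 1.1 kg (tan) to 6.5 kg (gold).

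On delivery, "all exercises will be performed by patients unsupervised", although "the cancer exercise specialists will check and advise on technique during weekly consultations". A separate document of exercise prescription principles, "written specifically for this study, will be used to guide the cancer exercise specialists", is mentioned but not reproduced in the article.

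**The concern.** The sentence is about where the band is held. Grip position fixes how much unstretched band lies between the hands. Because a band's load depends on stretch relative to that resting length, a longer segment taken through the same movement should pull less hard. The article says the opposite.

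If a specialist or patient used the sentence to adjust load, the load would move the wrong way. Widening the grip to progress would make the exercise easier, and narrowing it to ease off would make it harder. The second case is the less comfortable one. Patients exercise unsupervised, the programme lets them adjust training variables themselves when symptoms change, and the Introduction names shoulder weakness and pain among the barriers to exercise in this population. Nothing in the quantitative analysis is at stake.

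**Working it through.** The plan gives no figure for the effect of grip, so there is none to reproduce. The check is of direction, followed by an illustration of size.

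**Inputs from the protocol article (Study intervention).** Load is rated at 100% elongation. The colours are tan 1.1, yellow 1.3, red 1.7, green 2.1, purple 2.6, black 3.3, silver 4.6 and gold 6.5 kg.

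**Assumptions, not in the article.** Force rises with elongation. The grip lengths, travel and force exponents below are chosen for illustration.

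**Direction.** Let L0 be the unstretched band between the hands and e the elongation, e = stretch / L0.

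- Same end position L: e = (L − L0) / L0 = L/L0 − 1, which falls as L0 rises.
- Same travel d: e = d / L0, which falls as L0 rises.
- Stretch proportional to grip (d = c × L0): e = c, which does not change.

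A wider grip would raise e only if the stretch grew more than in proportion to the grip, which is no longer the same movement. A band anchored at its middle, under the feet or behind the back, behaves in the same way, because a wider grip leaves more free band.

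**Size, first set of lengths.** The reference is a 40 cm grip stretched to 80 cm, so e = 100% and the red band gives 1.7 kg. Force is proportional to e.

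| Grip L0 | Same 80 cm end point | Red band | Same 40 cm travel | Red band |
|---|---|---|---|---|
| 30 cm | 50/30 = 166.7% (+66.7%) | 2.83 kg | 40/30 = 133.3% (+33.3%) | 2.27 kg |
| 40 cm | 40/40 = 100% | 1.70 kg | 40/40 = 100% | 1.70 kg |
| 50 cm | 30/50 = 60% (−40%) | 1.02 kg | 40/50 = 80% (−20%) | 1.36 kg |

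If force rises only with the square root of e, the changes shrink but keep their sign. At 50 cm they are √0.6 − 1 = −22.5% (same end point) and √0.8 − 1 = −10.6% (same travel). At 30 cm they are √1.667 − 1 = +29.1% and √1.333 − 1 = +15.5%.

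**Size, second set of lengths.** The red band is held at 40, 60 and 80 cm, with force = 1.7 × e^k.

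| k | Same 120 cm end point: 40 / 60 / 80 cm | Same 60 cm travel: 40 / 60 / 80 cm |
|---|---|---|
| 0.6 | 2.58 / 1.70 / 1.12 kg | 2.17 / 1.70 / 1.43 kg |
| 1.0 | 3.40 / 1.70 / 0.85 kg | 2.55 / 1.70 / 1.275 kg |
| 1.4 | 4.49 / 1.70 / 0.64 kg | 3.00 / 1.70 / 1.14 kg |

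In every row the load falls as the grip widens.

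**Scale.** From the article's colour list, one step up adds 18.2% (1.3/1.1 − 1), 30.8%, 23.5%, 23.8%, 26.9%, 39.4% and 41.3% (6.5/4.6 − 1). One step down removes between 15.4% (1.1/1.3 − 1) and 29.2% (4.6/6.5 − 1). Under the linear assumption, a 10 cm change of grip from 40 cm can therefore matter as much as a change of band.

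**The case against.** The strongest reply is that the sentence is condensed table text with another reading: hands drawn further apart during the movement stretch the band more and so raise resistance. On that reading it is true, and the article does not describe the band set-up or fix a grip length. This does not rescue the wording. The sentence follows an instruction about hand placement and repeats that the hands are on the band, and the alternative reading would give no reason to standardise placement. At most the sentence would be ambiguous, and the same correction would cure that.

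It is also fair to say that no other statement in the article contradicts the sentence outright. The error is inferred from the elongation rating plus the assumption that force rises with elongation. The sizes depend on chosen lengths, and one case (stretch proportional to grip) shows no change. All of this stands, but none of it reverses the direction.

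What carries most weight is that the operative instruction, to standardise hand placement, is right whichever way grip acts. Progression runs through repetitions and then added resistance, for which eight graded colours are available, and nobody is told to set load by grip. Qualified specialists deliver the programme, with technique instruction beforehand and weekly checks, and a load that is too heavy should show as a shortfall against the target repetitions. These points limit the harm, though not completely, since the weekly contact may be by telephone, where grip cannot be seen. Perceived exertion is a weaker safeguard here, because Table 2 ties its exertion bands to aerobic intensity.

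**Conclusion.** The concern holds. As written, Table 2 gives the wrong direction: for the same movement a wider grip lowers band resistance, or at best leaves it unchanged. This rests on reading the sentence as being about where the band is held, which its wording supports, and on force rising with elongation. It does not depend on the illustrative lengths. Those put the effect of moving from a 40 cm to a 50 cm grip at −11% to −40%, and of moving to 30 cm at +15% to +67%, across the square-root and linear cases with fixed travel or fixed end point.

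Severity is minor. Harm arises only if someone uses the sentence to adjust load, which the plan does not ask for. Retention, the adherence outcomes, the sample size and the progression criteria are untouched.

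**What to change.** Replace the sentence in Table 2 with, for example: *For the same movement, gripping the band with the hands closer together raises the resistance, and gripping it with the hands further apart lowers it.* Keep the instruction to standardise hand placement.

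Check whether the exercise prescription principles document and the patient instructions carry the same statement, and correct them only if they do.

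The cost is one sentence, a check of the linked documents and a short note to the three cancer exercise specialists.
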